**Methods:**

This is the study protocol for a proof-of-concept, double-blind, randomized, controlled trial to be conducted between April 2026 to July 2028 at the maternity units of the two teaching hospitals in Lagos, Nigeria. At baseline, n = 153 sexually active women aged 18 years or older diagnosed with early-onset preeclampsia at 24–34 weeks’ gestation will be randomised to receive either daily oral tablet containing 600 mg of NAC or a placebo tablet that is matched for appearance and the dosing regimen in addition to standard antenatal care from diagnosis (randomisation) until either 34 weeks’ gestation or delivery, whichever comes first. The primary endpoint is the time-to-progression (in days) of early-onset preeclampsia to severe disease. The data analysis will be conducted on an intention-to-treat basis. Kaplan-Meier estimates with a Log-rank test will be used to calculate and compare the time-to-disease progression for the treatment groups, while Cox proportional hazard models with a backwards conditional method will be used to compare the primary endpoint between the treatment arms while adjusting for other covariates for precision using hazard ratios (HRs) and 95% confidence intervals (95%CIs). Subgroup analyses will also be performed to assess the differential effects of significant covariates on the impact of NAC on disease progression. Statistical significance will be reported as *P* < 0.05.

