### Sample size calculation

The sample size was calculated assuming a 1:1 randomization ratio, a two-sided type I error rate (α) of 0.05, and 80% statistical power to detect a hazard ratio of 0.5 between the NAC and placebo groups, based on an estimated 33.3% baseline probability of disease progression among pregnant women with early-onset preeclampsia [24]. Allowing for an anticipated 15% loss to follow-up or missing outcome data, the total planned sample size is 153 participants, who will be randomly allocated in equal proportions to the two study arms (approximately 76–77 participants per group).

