### Randomization and allocation concealment

Participants will be randomly assigned using a 1:1 block random sequence of 4–6 blocks generated by the study statistician from Random Allocation software version 1.0 (May 2004) prepared in advance of the trial to receive either a daily oral tablet containing 600 mg of NAC or a placebo tablet to match the NAC tablets in size, shape, colour, and overall appearance to maintain blinding in addition to standard antenatal care from diagnosis (randomisation) until either 34 weeks’ gestation or delivery, whichever comes first [Fig 1]. The active drug (NAC) and placebo tablets will be packed in identical, coded, transparent dispensing sachets by the onsite pharmacy technician. The technician will then store the coded randomisation list in a sealed, opaque envelope, which will be kept in a locked file cabinet at the study site until the end of the study. The 600 mg oral daily dosage of NAC was selected after a careful review of the literature on the effectiveness of NAC in exerting antioxidant, anti-inflammatory, and antiproliferative effects while maintaining a favourable safety profile [16–21]. Furthermore, a low dose of 600 mg daily aligns with widely available commercial formulations that offer better gastrointestinal tolerability, which is important for sustained adherence in our study population and will also simplify procurement and ensure consistent dosing during the study. The placebo tablets will be composed of inert excipients, including microcrystalline cellulose, lactose, and magnesium stearate, and will contain no active pharmacological ingredient. Given the characteristic sulfur-like odour and taste of NAC, both NAC and placebo tablets will be administered with Coca-Cola Zero Sugar immediately prior to ingestion to mask any sensory differences and minimize the risk of unblinding. Participants, investigators, and outcome assessors will remain blinded to treatment allocation throughout the study period. To evaluate the effectiveness of blinding, a blinding assessment will be conducted at the end of the intervention period. Participants and study personnel will be asked to indicate their perceived treatment allocation (NAC, placebo, or unsure). The success of blinding will be assessed by comparing the distribution of guesses between groups against that expected by chance. All study participants, irrespective of treatment arm allocation, will receive standard-of-care management for early-onset preeclampsia in accordance with the institutional protocol and internationally accepted guidelines. The study intervention will only be administered as an adjunct to standard care, which will include corticosteroids for fetal lung maturation, antihypertensive treatment, magnesium sulphate for seizure prophylaxis (when indicated), close maternal and fetal monitoring, and delivery based on standard clinical indications.

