### Data management and statistical considerations

Data will be collected prospectively with continuous data entry and checking. Queries will be actively pursued to ensure prompt clarification. Data will be entered into the REDCap database and then exported to Stata version 18.0 for Windows (StataCorp LLC, Texas, USA) for statistical analyses. Missing or incomplete data will be handled by running a missing values analysis using pairwise or listwise deletion if no pattern is detected or the multiple imputation method if a pattern is detected [26]. The primary analysis will be conducted on an intention-to-treat basis. The effectiveness of blinding will be evaluated using descriptive statistics and by comparing the proportion of correct guesses between study arms using the Chi-square test. Kaplan-Meier estimates with a Log-rank test will be used to calculate and compare the time-to-disease progression for the treatment groups while considering deliveries without preeclampsia with severe features as censored observations. We will then perform Cox proportional hazard models with a backwards conditional method to compare the study outcomes between the treatment arms while adjusting for other covariates using hazard ratios (HRs) and 95% confidence intervals (95%CIs). We will assess the calibration or goodness-of-fit statistic of the final model using the Hosmer-Lemeshow test, while the model’s explanatory power will be reported with Nagelkerke’s pseudo-R². Subgroup analyses will also be performed to assess the differential effects of significant covariates on the impact of NAC on disease progression. With oversight from the DSMC, two interim analyses of efficacy and futility for the primary outcome (progression to severe disease) will be conducted at 50% and 75% enrolment using O’Brien-Fleming stopping criteria [27] at cutoff *p*-values of less than 0.013 and 0.025, respectively

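### The only named test of blinding compares correct-guess rates between arms. It cannot see equal unblinding of both arms and reacts to one-sided guessing, so it does not carry out the protocol's own comparison with chance.

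*Protocol article*

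**What the plan says.** The protocol article describes the blinding assessment in two places.

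- *Randomization and allocation concealment*: participants and study personnel will be "asked to indicate their perceived treatment allocation (NAC, placebo, or unsure"), at the end of the intervention period. The criterion follows: "The success of blinding will be assessed by comparing the distribution of guesses between groups against that expected by chance".
- *Data management and statistical considerations*: "The effectiveness of blinding will be evaluated using descriptive statistics" and by "comparing the proportion of correct guesses between study arms using the Chi-square test".

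The first section sets chance as the benchmark and records three possible answers. The second names the only inferential test. That test makes no comparison with chance, and the section does not say how unsure answers enter it. Neither section says which chi-square result would count as success or failure. The abstract sets the general significance level: "Statistical significance will be reported as *P* < 0.05".

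**The concern.** Blinding holds, in the sense of the randomisation section, when guesses are unrelated to allocation. The named test has another null hypothesis: that the proportion of correct guesses is the same in both arms. A correct guess means NAC in one arm and placebo in the other, so the two hypotheses come apart. Equal unblinding of both arms satisfies the test's null. Guesses that carry no information but lean to one treatment violate it.

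This matters because the protocol itself recognises an unblinding risk, the sulfur-like odour and taste of NAC, and relies on a masking drink. Odour could inform both arms, by its presence in one and its absence in the other, and that is the pattern the test cannot see. The primary composite includes headache, visual disturbance and dyspnoea, which participants also record in a daily diary. Readers will use the blinding result to judge how far those components can be trusted.

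**Working it through.** The plan gives no figure for this test, so there is none to reproduce. The check asks how the test behaves at the planned size.

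**Inputs from the protocol article**

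- Arm sizes 77 and 76: "approximately 76–77 participants per group" (*Sample size calculation*), with everyone assumed to answer.
- Significance level 0.05 (abstract, Methods).
- Answers: NAC, placebo, unsure.

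**Assumed.** The documents give no expected guess distribution, so a range is shown. Unsure counts as not correct. Pearson chi-square is used without continuity correction.

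**Step 1: what the test compares.** Let g and h be the probabilities of guessing NAC and placebo. If guesses are unrelated to allocation, both are the same in each arm, so

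- P(correct | NAC arm) = g
- P(correct | placebo arm) = h

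The test then asks whether g = h, that is, whether guesses lean. If instead both arms guess correctly with the same probability c, the difference is c − c = 0 for any c, and the test rejects only at its nominal rate.

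**Step 2: how often each test gives p < 0.05.** 4,000 simulated trials per row. The comparator is a chi-square test of guess (three categories) by arm, which does test association with allocation.

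| Assumed guesses | Named test | Guess by arm |
|---|---|---|
| Unrelated to allocation, NAC/placebo/unsure 40/40/20 | 5% | 5% |
| Unrelated, 45/35/20 | 24% | 5% |
| Unrelated, 50/30/20 | 72% | 5% |
| Unrelated, 60/20/20 | about 100% | 5% |
| 75% correct in both arms | 5% | about 100% |
| 90% correct in both arms | 5% | about 100% |
| 95% correct in both arms | 4% | about 100% |
| NAC arm only unblinded (95% v 40% correct) | about 100% | about 100% |

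Excluding unsure answers leaves the pattern unchanged (for example 28% at 45/35/20 and 80% at 50/30/20).

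**Step 3: single tables.**

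- *60/20/20 in both arms.* Correct: 46/77 v 15/76. Overall 61/153 = 0.399. Difference 0.597 − 0.197 = 0.400. Standard error = √[0.399 × 0.601 × (1/77 + 1/76)] = 0.0792. Chi-square = (0.400/0.0792)² ≈ 25.5, p = 4 × 10⁻⁷. Guess by arm, 46/15/16 v 46/15/15: p = 0.99.
- *70/30/0 in both arms.* Correct: 54/77 v 23/76, p = 8 × 10⁻⁷. Guess by arm: p = 0.96.
- *About 90% correct in both arms, no unsure answers.* Correct: 69/77 v 68/76, 0.896 v 0.895, p = 0.98. Guess by arm: p = 1 × 10⁻²².

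**Step 4: Bang's index per arm**, (correct − incorrect) / all asked, unsure included in the denominator.

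- 60/20/20: NAC (46 − 15)/77 = +0.40; placebo (15 − 46)/76 = −0.41. Opposite signs and a sum near zero show a common lean, not knowledge of allocation.
- About 90% correct: NAC (69 − 8)/77 = +0.79; placebo (68 − 8)/76 = +0.79. Both clearly positive: unblinded.

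**The case against.** **The false alarm is conditional.** A reader might infer that the test signals failure whenever guesses are unrelated to allocation. It does not. With an even NAC/placebo split it rejects at its nominal 5%, and with a mild lean (45/35/20) in 24% of trials. The problem needs a lean, and no document says how large a lean to expect. This stands. The insensitivity to equal unblinding needs no such condition.

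**The test is not the whole evaluation.** Descriptive statistics are planned too. If they include the proportions correct, 69/77 and 68/76 would tell any reader that blinding had failed, whatever the p-value. It would therefore be too strong to say that the planned evaluation as a whole must give the wrong answer. This stands, but the content of the descriptive part is not stated and no criterion is attached to it.

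**No decision rule is stated.** Reading p < 0.05 as failed blinding is natural, but it is an inference. The only section that speaks of success uses chance as its benchmark, which is the right idea. This also stands, and it is why the point is a mismatch between two sections rather than a wrong success rule.

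**Nothing else depends on the result.** Blinding assessment is not a listed outcome, and no stopping rule or primary analysis uses it. Masking itself comes from matched tablets, the masking drink and blinded assessors. A reader might infer that the trial's efficacy result is at risk; the log-rank and Cox analyses are unchanged by this point.

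**It is not a detail left to an analysis plan.** The article names a specific test, and that test does not match the criterion the article sets.

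**Conclusion.** The point holds in a limited form. The only named test of blinding answers a different question from the one the randomisation section poses. Its blind spot for equal unblinding follows from its definition and would not shrink with a larger sample. Its tendency to flag uninformative guesses depends on the lean, and runs from the nominal rate with balanced guesses to near certainty at 60/20/20.

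The percentages rest on assumed guess distributions, on everyone answering, and on arms of 77 and 76. The direction of the two errors does not depend on those choices. As a supporting analysis this deserves correction before results are seen, but it is not critical: what it affects is the interpretation of the symptom-based parts of the composite.

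**What to change.** In *Data management and statistical considerations*, replace the chi-square test of correct guesses with a measure of association between guess and allocation that keeps the unsure answers. Either of these serves:

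- a blinding index for each arm (such as Bang's) with 95% confidence interval, the two arms read together so that a common lean is told apart from unblinding; or
- a chi-square test of guess (NAC, placebo, unsure) by arm, with the full table of guesses shown.

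Run it separately for participants and for study personnel, and use the same criterion, comparison with chance, in *Randomization and allocation concealment*. Keep the descriptive statistics and state that they include the guess distribution in each arm.

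The cost is one sentence in the analysis section and a matching phrase in the randomisation section. No new data are needed, since the three answers are already to be collected, and recruitment had not begun when the article was submitted.

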## Introduction

Preeclampsia is a progressive multisystemic complication of pregnancy characterized by hypertension and often proteinuria, typically occurring after 20 weeks of gestation [1]. It affects approximately 2–8% of pregnancies globally [2] and up to 16.7% among pregnant women in Nigeria [3]. Preeclampsia remains a leading cause of maternal and perinatal morbidity and mortality worldwide, particularly in low- and middle-income countries [4]. Preeclampsia with severe features represents an escalation of preeclampsia severity and is associated with a higher risk of adverse maternal and fetal outcomes [2,5]. Severe features of preeclampsia include a systolic blood pressure of at least 160 mmHg or a diastolic blood pressure of at least 110 mmHg, thrombocytopenia, impaired liver function, severe persistent right upper quadrant pain, progressive renal insufficiency, pulmonary oedema, and new-onset cerebral or visual disturbances [6].

Despite significant advancements in obstetric care, the incidence of preeclampsia remains a substantial public health challenge [7] and effective strategies to prevent the disease progression remain limited, particularly in low-resource settings. While certain interventions, such as low-dose aspirin prophylaxis [8] in high-risk women, have shown some efficacy in reducing the risk of preeclampsia, there remains a need for additional measures to prevent the development of severe disease in women with early-onset preeclampsia, particularly in resource-constrained settings where the burden of disease is greatest [4]. Currently, the only cure for preeclampsia is delivery of the fetus and placenta [7,9] however, this is commonly associated with iatrogenic preterm delivery. To prevent this complication and improve maternal and perinatal outcomes, research efforts are currently focused not only on the prevention of preeclampsia but also on its treatment and prevention of its severe features.

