### Study outcomes

The primary outcome measure was time-to-disease progression (in days) among women with early-onset preeclampsia, defined as the interval from diagnosis to the first occurrence of a composite endpoint indicating clinical deterioration. Disease progression is defined as the development of any of the following: consistently elevated blood pressure of 160/110 mmHg or higher; severe proteinuria of 3+ or a urine protein/creatinine ratio of 0.3 or higher; platelet counts less than 100,000/µL; elevated liver enzymes (AST/ALT) or evidence of hepatic dysfunction; serum creatinine level greater than 1.1 mg/dL or doubling of baseline creatinine in the absence of other renal diseases; symptoms and signs of pulmonary oedema such as dyspnoea and crackles on lung auscultation; cerebral or visual disturbances such as headaches, visual disturbances, altered mental status, seizures (eclampsia), or other neurological symptoms; and evidence of placental dysfunction such as placental abruption, fetal growth restriction or oligohydramnios on ultrasound examination [2,5]. Participants who do not experience disease progression will be censored at delivery or at the end of follow-up. Secondary outcomes will include (1) safety and treatment tolerability, (2) maternal outcome (maternal mortality), and (3) composite neonatal outcomes, including low birth weight in term neonates (baby’s birth weight less than 2500g), IUGR, stillbirth, NICU admission, and perinatal and neonatal mortality. Women who develop preeclampsia with severe features will be managed as per the obstetric unit protocol and will be excluded from further participation in the study.

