
**Fig 1 pone.0347695.g001:**
[figure not shown]
Trial flow chart.

**Follow-up evaluations:** Data collection will commence on the day the participant is randomized into the trial and will continue until the trial is terminated or the participant withdraws from the trial at any time for any reason. Study visits will be scheduled every two weeks until 32 weeks and weekly thereafter until delivery [Table 1]. Participants will be monitored using a daily symptom diary to record features of severity—headaches, visual disturbances (e.g., blurred vision, scotoma), dyspnoea, and right hypochondria or epigastric pain and any adverse event—gastrointestinal upset, dry mouth, nausea, vomiting, diarrhoea, rash, and fatigue and its severity using a daily symptom diary and present this for recording at their next clinic visit. At every follow-up visit, a newly filled dispensing sachet containing the experimental drugs with the same numeric code will be given to each woman, and the pills remaining in used sachets are then counted to assess adherence. Adherence will be defined as the use of at least 70% of the prescribed tablets for each participant. Allocations to treatment arms will be concealed from the study investigators, clinic staff, and trial statistician using sealed opaque envelopes that are sequentially numbered. The onsite pharmacy technicians will not be involved in the design, conduct, statistical analysis, and reporting of study findings. Additional information to be collected during the follow-up visits includes a history of allergies, level of treatment adherence, drug tolerability, bedside urinalysis for albumin, venous blood samples for biweekly measurements of haemoglobin, creatinine, liver enzymes (AST/ALT), and complete blood count. Serum biochemical assessments of glutathione and homocysteine levels will be performed at randomisation (baseline) and at weeks 28 and 32. Fetal growth scans and umbilical artery velocimetry (from 32 weeks) will also be done biweekly until delivery. At delivery, data on gestational age (in weeks), total duration of experimental drug intake (in days), intrauterine growth restriction (IUGR), neonatal birth weight (in grams), neonatal status at birth, 7th- and 28th-day (dead/alive), neonatal intensive care unit (NICU) admission, and length of NICU admission (in days) will be collected and recorded in the electronic CRF. Cord blood sampling at delivery for analysis of glutathione and homocysteine levels will also be collected to provide additional insight into maternal-fetal antioxidant transfer and potential downstream effects of NAC [Table 1].

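### Kaplan-Meier with delivery as ordinary censoring overstates the probability of progression; the size depends on delivery timing and on an end of primary follow-up that is not fixed

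*Protocol article*

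**What the plan says.** In the section Data management and statistical considerations, the protocol article states that "Kaplan-Meier estimates with a Log-rank test will be used to calculate and compare the time-to-disease progression" between arms, "considering deliveries without preeclampsia with severe features as censored observations". Cox models then give hazard ratios. The section Study outcomes repeats the rule: "Participants who do not experience disease progression will be censored at delivery or at the end of follow-up".

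Three other places bear on it:

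- The Introduction describes delivery as the only cure and adds that "this is commonly associated with iatrogenic preterm delivery".
- Under Randomization and allocation concealment, standard care includes "delivery based on standard clinical indications", and study tablets are given "until either 34 weeks’ gestation or delivery, whichever comes first".
- The follow-up paragraph says "Study visits will be scheduled every two weeks until 32 weeks and weekly thereafter until delivery", whereas Table 1 marks the primary endpoint only up to 34 weeks.

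No competing-risk estimator is named. The censoring rule is stated twice, so this is a choice the article makes and not a detail left to a later analysis plan.

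**The concern.** Kaplan-Meier treats a censored woman as someone who could still progress later at the same rate as those who remain under observation. That suits a woman lost to follow-up. It does not suit a woman who has delivered, because antenatal progression is then no longer possible. With deliveries censored, 1 minus Kaplan-Meier describes progression in a hypothetical setting where nobody delivers. It exceeds the actual probability of progression whenever some women deliver first.

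Two things are at stake. The first is absolute risks and medians, which readers of a trial about delaying progression will want and which the plan proposes to calculate this way. The second is how the hazard ratio is read. If NAC also shifts the timing of delivery, a cause-specific hazard ratio does not by itself show whether fewer women progress.

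**Working it through.** **Inputs from the article.** Baseline progression probability 33.3%, hazard ratio 0.5, 80% power, two-sided alpha 0.05, 15% loss and 153 women (Sample size calculation); eligibility at 24–34 weeks. The article gives no frequency or timing for delivery without progression, so these are assumed below and shown as a range.

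**How firm is the 33.3%?** The stated 153 does not follow if 33.3% is the control progression probability. The NAC probability is then 1 − (1 − 0.333)^0.5 = 0.183, the mean is 0.258, and Freedman's 71 events need 276 women, or 325 after 15% loss. The figure 153 appears if 33.3% is read as event-free survival: mean event probability 0.545, 71/0.545 ≈ 130, and 130/0.85 ≈ 153. That is a separate issue, but it means the 33.3% should be used with care here.

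**Closed form, constant hazards.** Let p be the proportion who have progressed and d the proportion who have delivered without progression by a given time, with q = p + d. The true cumulative incidence is p, and 1 − KM = 1 − (1 − q)^(p/q). For p = 33.3%:

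| d | 1 − KM | Excess (points) |
|---|---|---|
| 5% | 34.3% | 1.0 |
| 10% | 35.4% | 2.1 |
| 20% | 37.9% | 4.6 |
| 30% | 41.0% | 7.7 |
| 40% | 45.1% | 11.8 |
| 50% | 51.1% | 17.8 |
| 60% | 61.9% | 28.6 |

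Example for d = 20%: q = 0.533, p/q = 0.625, and 1 − 0.467^0.625 = 0.379.

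**Sensitivity to the meaning of 33.3%.** If one third of exits are progressions, then at q = 0.75 the incidence is 0.25 against 1 − 0.25^(1/3) = 0.370. If two thirds are, it is 0.50 against 1 − 0.25^(2/3) = 0.603. The excess is 12.0 and 10.3 points respectively, so the problem exists under either reading.

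**Simulation with delivery tied to gestational age.** Assumptions: entry uniform over 24–34 weeks; mean delivery at 35, 36 or 37 weeks (spread 2, 1.5 and 1 week); a constant progression hazard set so that about one third progress within the follow-up in question. That calibration is why the 34-week column runs higher. Each cell gives 1 − KM against true cumulative incidence, with the excess in points:

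| Mean delivery | Stop at 34 weeks, week 8 | To delivery, week 8 | To delivery, week 12 |
|---|---|---|---|
| 37 | 50.9 vs 50.9 (0.0) | 34.3 vs 29.4 (4.9) | 47.0 vs 33.3 (13.7) |
| 36 | 51.3 vs 48.7 (2.6) | 38.6 vs 30.4 (8.2) | 52.0 vs 33.4 (18.6) |
| 35 | 53.8 vs 44.4 (9.4) | 44.1 vs 31.2 (12.9) | 58.0 vs 33.4 (24.6) |

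In the 34-week scenario 0.1% to 22% deliver before 34 weeks without progression. With follow-up to delivery, the excess at week 4 is at most 3.6 points (25.1 vs 21.5). When delivery is also linked to severity, the follow-up-to-delivery excess is about 5 to 12 points at week 8 and 12 to 20 at week 12.

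**Medians.** In the middle row, Kaplan-Meier passes 50% by week 12 although only 33.4% have progressed. A median would be reported where none exists.

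**Test validity.** With 130 women, 4,000 runs and no effect on progression, log-rank type I error was 5.3% and 4.7% (without and with a severity link). When NAC delayed delivery by one week it was 5.7% and 5.5%. The Monte Carlo standard error is √(0.05 × 0.95/4000) = 0.34 points, so these lie near the nominal level.

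**Why the hazard ratio alone is not enough (illustrative hazards).** Take placebo hazards of progression to delivery as 1:2, so 1/3 eventually progress. If NAC halves progression only, 0.5/(0.5 + 2) = 20% progress. If it halves both, 0.5/(0.5 + 1) = 33.3% progress. The cause-specific hazard ratio is 0.5 in both cases.

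**The case against.** The strongest reply is that the efficacy result is a log-rank test and a Cox hazard ratio, and both survive. That stands. For a proof-of-concept question about delaying progression, the cause-specific hazard is a reasonable target. A reader might infer that the primary test is invalid; neither the theory nor the simulation supports that.

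A second reply is that the article gives no delivery rate. That also stands. A reader might take the 33.3% to mean that two thirds of placebo women end follow-up by delivery, and so conclude that the bias must be substantial. The article does not say this: 33.3% has no stated horizon, its meaning is uncertain, women may also be censored at the end of follow-up, and 15% loss is allowed for. The largest excesses also sit in the tail. With about 76 women per arm, 90% having progressed or delivered leaves about 8 at risk, before losses.

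Third, a reader might infer that the censored deliveries are mainly disease-driven, with deteriorating women removed just before the threshold. This is only partly supported. The composite in Study outcomes already counts severe hypertension, organ dysfunction, eclampsia, abruption, growth restriction and oligohydramnios as events, so most disease reasons for delivery are events. Some doubt remains because the analysis section and Table 1 refer only to severe features, and the Introduction's list of these has no placental items. How often this would matter is not given.

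Finally, Fine-Gray and sensitivity analyses by indication are commonly left to an analysis plan. Their absence is not the point here.

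**Conclusion.** The point holds for the absolute scale. As written, 1 minus Kaplan-Meier will exceed the true probability of progression whenever women deliver before progressing, and a median read from the curve will come too early or may not exist. The direction is certain; the size is not. Under the assumed delivery patterns without a severity link, the excess at 8 weeks is about 0 to 9 points if primary follow-up stops at 34 weeks. If follow-up runs to delivery, it is about 5 to 13 points at 8 weeks and 14 to 25 at 12 weeks. These ranges rest on assumed mean delivery at 35–37 weeks, uniform entry, a constant progression hazard and about one third progressing. The hazard ratio and log-rank test are sound as cause-specific comparisons, but they do not translate directly into absolute risk. This should be corrected because the rule is explicit and easy to change; it does not threaten the primary test.

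**What to change.** In Data management and statistical considerations:

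1. Replace the Kaplan-Meier estimates with Aalen-Johansen cumulative incidence of progression by arm, with delivery or death without progression as the competing event. Take absolute risks from these curves, and report a median only if the cumulative incidence reaches 50%.
2. Keep the log-rank test and Cox model, and label them as comparisons of the cause-specific hazard of progression.
3. Show the cause-specific hazard or cumulative incidence of delivery without progression by arm, so that any effect of NAC on delivery timing is visible.
4. State one end of primary follow-up and use it consistently in Study outcomes, Table 1 and the analysis section.

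A Fine-Gray model may be added as supportive. A sensitivity analysis by reason for delivery is optional. It would need the indication for delivery, which is not among the listed delivery data, and a rule for classifying it.

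The cost is revised wording and one extra analysis in Stata. Recruitment had not begun at manuscript submission, so the estimator can be fixed before outcome data exist.

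### The article's two descriptions of the Cox step conflict on scope; applied to the neonatal composite with the clock defined for the primary outcome, the hazard ratio would largely reflect time to delivery

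*Protocol article*

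**What the plan says.** Two places in the protocol article describe the Cox step.

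- Abstract, Methods: "Cox proportional hazard models with a backwards conditional method will be used to compare the primary endpoint between the treatment arms".
- Data management and statistical considerations: "We will then perform Cox proportional hazard models with a backwards conditional method to compare the study outcomes between the treatment arms", reported as hazard ratios with 95% confidence intervals. The only other between-arm tests named there are the log-rank test, for time to progression, and a chi-square test, for the blinding guesses.

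Under Study outcomes, the neonatal secondary outcome is given as "composite neonatal outcomes, including low birth weight in term neonates", followed by "IUGR, stillbirth, NICU admission, and perinatal and neonatal mortality". The follow-up text has birth weight, growth restriction and NICU admission recorded at delivery, and vital status recorded at birth, day 7 and day 28.

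A time origin is given only for the primary outcome, "defined as the interval from diagnosis to the first occurrence of a composite endpoint", and so is a censoring rule (delivery or end of follow-up). Neither is given for the neonatal outcomes.

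**The concern.** The abstract's scope is the primary endpoint. The statistical section's scope is all study outcomes, so as worded it assigns a hazard ratio to the neonatal composite.

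That composite is mainly a yes/no outcome settled at birth or within 28 days of it. Growth restriction and stillbirth are partial exceptions, since either can arise before delivery. With a clock running from diagnosis, most women would have their event or their censoring at about the date of delivery. The model would then compare how fast affected babies are delivered per day, whereas the clinical question is what share of babies is affected. The two answers differ whenever the arms differ in time to delivery. The trial hopes to delay progression, and the article describes delivery as the only cure, so a difference in delivery time is a plausible result of a working drug. At stake is a reported neonatal benefit that is only a later birth.

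**Working it through.** The article gives no figure for the neonatal analysis, so there is none to reproduce. The check asks what the Cox model returns when the neonatal risk is the same in both arms.

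**Inputs from the article.** Placebo progression 33.3%; hazard ratio for progression 0.5; two-sided alpha 0.05; N = 153 with 15% loss, so 153 × 0.85 ≈ 130 evaluable women.

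**Assumptions, not in the article.** Delivery 3 days after progression; otherwise a mean of 42 days to delivery; composite risk p of 50% or 70%, equal in both arms and unrelated to the time of delivery.

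**Mechanism.** Let g(t) be the delivery hazard in an arm. If a share p of babies is affected and unaffected births are censored at delivery, the hazard of an affected birth is p × g(t). With equal p, the neonatal hazard ratio is p·g(NAC) / p·g(placebo), which is the delivery hazard ratio.

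**Size, by hand.** Take exponential times and ignore the 3-day lag.

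- Delivery without progression: μ = 1/42 = 0.0238 per day.
- Placebo progression: λ/(λ + μ) = 1/3, so λ = μ/2 = 0.0119. On NAC: λ/2 = 0.0060.
- Delivery hazard ratio: (μ + λ/2)/(μ + λ) = 1.25/1.50 = 0.83.

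Simulation with the 3-day lag gives a median of about 0.84.

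**False-positive rate, by hand, at 0.84.** |ln 0.84| = 0.174, and the standard error is about 2/√(events).

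- p = 50%: 65 events, SE 0.248, z = 0.70; two-sided rejection ≈ 11%.
- p = 70%: 91 events, SE 0.210, z = 0.83; two-sided rejection ≈ 13%.

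Simulation gives about 10% and 12–13%, nearly all favouring NAC. With no difference in delivery time the same test rejects at about 5%. A comparison of proportions rejects in 4–6% throughout.

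**Dependence on clock and censoring.** A separate simulation used 76 women per arm and an assumed Weibull time to delivery (shape 1.5, scale 28 days), with equal risk p = 50% in both arms. Cells show the median hazard ratio and the rejection rate.

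| Assumed delivery HR | From randomisation, censored at delivery | From randomisation, censored at delivery + 28 days | Clock from birth |
|---|---|---|---|
| 1.0 | 1.01; 4% | 0.99; 4% | 1.01; 4% |
| 0.8 | 0.80; 16% | 0.91; 7% | 1.01; 4% |
| 0.67 | 0.67; 39% | 0.83; 13% | 1.00; 3% |
| 0.5 | 0.50; 82% | 0.72; 31% | 1.00; 5% |

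The bias follows the delivery hazard ratio when censoring is at delivery. It shrinks with day-28 censoring and is absent when the clock starts at birth.

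**The case against.** The strongest reply is that the problem hangs on one loose phrase. The abstract limits the Cox step to the primary endpoint, and almost everything around the sentence in the statistical section concerns progression: the Kaplan-Meier and log-rank analysis before it, a single final model after it, subgroups for the effect on progression, and interim looks at the primary outcome. On that reading the article has simply not given a method for the secondary outcomes, which a condensed article may leave to the full protocol or analysis plan. This stands as a reason not to treat neonatal Cox models as settled. It does not remove the conflict, because the sentence as written covers the study outcomes without restriction.

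Second, the article sets no clock for neonatal outcomes, and recording status at birth, day 7 and day 28 would suit a clock from birth. This also stands: the bias is conditional on carrying over the primary outcome's rule. That is, however, the only rule the article offers.

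Third, not every component is fixed at birth. Fetal growth restriction can be seen on antenatal scans, and fetal death can precede delivery. The statement therefore holds for most components only.

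A reader might also infer that false neonatal findings would be common, or that a true neonatal harm would be hidden. The documents do not support either. Rates well above 10–13% need more progression than the 33.3% planned, or a posited larger delay in delivery. The apparent masking of harm depends on the assumed shape of the delivery-time distribution, and nothing in the article fixes that shape.

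**Conclusion.** The concern holds in a conditional form. What is certain is that the abstract and the statistical section disagree on which outcomes the Cox model covers. What follows if the wider wording is applied to the neonatal composite, from diagnosis and with censoring at delivery, is a hazard ratio that largely reflects delivery timing: about 0.84, with about 10–13% false positives.

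Only the 33.3%, the hazard ratio of 0.5, the sample size and the alpha come from the article. The delivery times, the composite risk and its independence of delivery time are assumptions. A longer delay would enlarge the bias. The documents do not show that the trial will analyse neonatal outcomes this way. The primary comparison is unaffected. This should be corrected, but it is not a defect in the trial's main inference.

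**What to change.** In Data management and statistical considerations:

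- Restrict Kaplan-Meier, log-rank and Cox to the primary endpoint, as the abstract does.
- Compare the neonatal composite and its components as proportions by randomised arm, with risk ratio and risk difference and 95% confidence intervals (for example log-binomial or modified Poisson regression).
- Report gestational age at delivery separately, so that prolongation is shown as prolongation.
- State that delivery and neonatal data are still collected for women who progress. Study outcomes says that women who develop severe features take no further part in the study; read literally, that could remove their babies from the comparison.

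The cost is a few sentences. The variables are already planned for delivery and for days 7 and 28, and enrolment had not begun at submission. If the exclusion of progressors was meant to end data collection, follow-up of those births is an added task. The downside is that a neonatal benefit will be declared less often when the drug only delays birth.
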